# Effect of acupuncture with donepezil based on syndrome differentiation on cognitive function in patients with mild-to-moderate Alzheimer’s disease: a study protocol for a multicenter randomized controlled trial

**DOI:** 10.1186/s13063-022-06532-1

**Published:** 2022-08-19

**Keywords:** Alzheimer’s disease, Acupuncture, Syndrome differentiation, Randomized controlled trial, Study protocol

## Abstract

**Background:**

There has been a rapid increase in the worldwide prevalence of Alzheimer’s disease (AD). Previous studies have shown that acupuncture can improve neurological and cognitive function; however, the utility of applying acupuncture in patients with AD remains unclear. This study protocol describes a clinical trial for evaluating the efficacy and safety of acupuncture based on syndrome differentiation with donepezil hydrochloride on cognitive function in patients with AD.

**Methods/design:**

This multicenter randomized controlled trial commenced on February 1, 2019, at the Shanghai Longhua Hospital of TCM, Shanghai Huashan Hospital of Fudan University, and Shanghai Mental Health Center, and will conclude on June 30, 2022. The study will recruit 184 patients randomly divided into an acupuncture group or a control group at a 1:1 ratio. All participants will receive donepezil hydrochloride (5 mg/day), and those in the acupuncture group will receive acupuncture based on syndrome differentiation with donepezil for 12 weeks. The primary outcome will be the post-treatment change in the Alzheimer’s Disease Assessment Scale-cognition score at 12 weeks. The secondary outcomes will be the efficacy scores of the Minimum Mental State Examination, Alzheimer’s Disease Cooperative Research Activity-Daily Life, and Quality of Life-Alzheimer’s Disease. All assessments will be performed at baseline, after treatment (week 12), and at follow-up (weeks 24 and 36).

**Discussion:**

This trial may provide high-quality evidence for the efficacy of acupuncture in the treatment of AD. The results of this study will be published in peer-reviewed journals.

**Trial registration:**

ClinicalTrials.govNCT03810794. Registered on 17 January 2019.

## Introduction

### Background

The incidence of Alzheimer’s disease (AD) is increasing worldwide [1], and the aging of the population in particular will accelerate this trend. According to statistics, there are about 7 million people with AD [2], which is the eighth leading cause of death, causing a heavy burden on families and society [3]. In China, the treatment burden of AD has reached $167.74 billion in 2015, accounting for 1.47% of the gross domestic product, and it is expected to reach $2.11 trillion worldwide in 2030 [4]. Unfortunately, it is estimated that by 2050, the number of population over 65 in China will reach 400 million [5]. If calculated based on the prevalence rate of 8.2/1000 person-years over 65 [6], the prevention and treatment of AD will undoubtedly bring a heavy burden to China by 2050.

AD mainly manifests as hippocampal amnesia syndrome. It is characterized by episodic memory impairment, coupled with changes in behavior and emotions as well as a significant reduction in patients’ daily life capability, social interaction, and work ability [7]. The pathophysiological mechanism of AD is complex and its pathogenesis has not yet been elucidated. Typical pathological features of AD include the deposition of extracellular β-amyloid (Aβ) to form senile plaques (SP), neurofibrillary tangles (NFT) composed of intracellular hyperphosphated tau protein, and synapse loss [8, 9]. The most effective treatment for AD involves promoting cholinergic neurotransmission and reducing acetylcholine hydrolysis in the brain [10–13]. Currently, the US Food and Drug Administration has only approved five medicines for AD. Four of the drugs are cholinesterase (AchE) inhibitors, while the fifth, memantine [14], is an inhibitor of the N-methyl-D-aspartic acid receptor (NMDA). A previous meta-analysis reported that taking one of the AchE inhibitors (donepezil hydrochloride) for 24–26 weeks reduced the Alzheimer’s Disease Assessment Scale-Cognitive Subscale (ADAS-cog) score of patients with mild-to-moderate AD by an average of 2.67 points [15]. However, considerable adverse effects of the medicines such as muscle cramps, weakness, nausea, vomiting diarrhea, and insomnia were also reported [16, 17].

Our previous study reviews [18] five non-pharmacological prevention strategies for AD and cognitive decline can effectively supplement drug therapies. Currently, non-drug treatments mainly include exercise intervention, cognitive intervention, music therapy, repetitive transcranial magnetic stimulation, and acupuncture therapy [19]. Among them, acupuncture therapy is a unique non-pharmacologic therapy which can improve the cognitive function of patients [20] through various mechanisms, such as protecting neurons, enhancing neurotransmission, reducing oxidative stress, and reducing Aβ protein deposition [21]. Studies indicate that acupuncture can regulate brain networks by increasing connectively between cognition-related regions, such as the insula, dorsolateral prefrontal cortex, hippocampus, thalamus, inferior parietal lobule, and anterior cingulate cortex, thereby improving cognitive function [22] and acupressure training improved cognitive function of old adults [23].

Recently, several clinical trials have shown that acupuncture can have a positive effect on patients with AD, including improving cognition [24–27]and memory [27, 28], as well as reducing the side effects of medications [29].

Preliminary achievement in experimental studies has been conducted on the mechanism of acupuncture treatment for AD. In amyloid precursor protein/presenilin-1(APP/PS1) transgenic mice, acupuncture reduced the deposition of β-amyloid precursor protein lyase 1 (BACE1), a key protein involved in the production of Aβ peptide; regulated the level of protein kinase A (PKA) and its related substrates (such as long-term potentiation [LTP]) [30]; upregulated the expression of brain-derived neurotrophic factor (BDNF), and promoted neurogenesis [31]. In Senescence-accelerated mouse prone 8 (SAMP8), acupuncture enhanced cell proliferation in dentate gyrus (DG) [32], reduced memory impairment, and increased the level of p-AMPK (phosphor-activated protein kinase) in the hippocampus [33]. Furthermore, in injected A*β1–40* rat model, acupuncture led to improved learning and memory function by suppressing the Notch signaling pathway in the hippocampus [34]. PET studies have shown that acupuncture can increase blood perfusion and metabolism in certain brain regions, including the right amygdala, right hippocampus and thalamus, and brain stem which may have a positive impact on cognition in ibotenic acid injection rats [35, 36].

In acupuncture clinic practice, doctors select varying acupoint formulas based on individual conditions, which are significantly affected by the heterogeneity of patients. Our previous study [37] on the research literature in the past 20 years has implied that heart qi deficiency and kidney essence deficiency are the main TCM syndromes of AD. A randomized controlled trial (RCT) on a formula for tonifying the SHEN (*kidney*) or XIN (*heart*) reported a minimum effective rate of 70.91% (using the Mini-Mental State Examination [MMSE]) after 48 weeks’ treatment in patients with mild-to-moderate AD [38]. However, few studies on acupuncture for AD have employed syndrome differentiation, which could have contributed to inconsistent findings. We previously conducted a retrospective study on 30 patients with mild-to-moderate AD who underwent acupuncture based on kidney or heart differentiation for 3 months in the Acupuncture Department of Longhua Hospital. After the 12-week treatment, the ADAS-cog score decreased by 4.04±4.23 points. These findings encouraged us to further evaluate the role of acupuncture therapy in AD treatment. This clinical trial will aim to evaluate the efficacy and safety of acupuncture based on syndrome differentiation with donepezil on cognitive function, activities of daily living, and quality of life in patients with mild-to-moderate AD. The findings of this clinical trial could contribute toward establishing a normalized program for the treatment of AD with acupuncture.

### Objectives

This study protocol aims to describe a clinical trial for evaluating the efficacy and safety of acupuncture with donepezil hydrochloride on cognitive function in patients with AD and to explore the role of acupuncture based on syndrome differentiation (heart qi deficiency, kidney essence deficiency) in the conventional treatment of AD.

### Trial design

This multicenter randomized controlled trial will be conducted from 1 February 2019 to 30 June 2022 in three hospitals. After preliminary screening, the participants will be randomly assigned to the acupuncture group (AG) or control group (CG) at a ratio of 1:1. This protocol was formulated in strict accordance with the SPIRIT reporting guidelines [39]. This trial registered identifier is NCT03810794 (www.ClinicalTrials.gov). The trial will strictly implement the principles of the “Declaration of Helsinki” (Edinburgh 2000). A flowchart of the trial is shown in Fig. 1.

**Fig. 1 Fig1:**
[figure not shown]
Flowchart of the trial: the participants will be randomly assigned to the acupuncture group (AG) or control group (CG) at a ratio of 1:1; all the patients will be treated for 12 weeks and be assessed at week 12, week 24, and week 36

## Methods/design

### Study setting

This trial will be conducted in three hospitals in Shanghai (Longhua Hospital Shanghai University of Traditional Chinese Medicine, Mental Health Center Shanghai Jiao Tong University School of Medicine, and Huashan Hospital Fudan University).

### Inclusion criteria

This study will include patients (1) aged 50–85 years; (2) who meet the AD diagnostic criteria of the National Institute of Neurological and Communicative Disorders and Stroke (NINCDS), and the Alzheimer Disease and Related Disorders Association [40]; (3) with cognitive impairment assessed using the MMSE (Chinese version), with scores ranging from 11–22 for those with primary school education and junior high school education or 11–26 for those with higher education; (4) having a Medial Temporal Lobe Atrophy Rating Scale score of ≥ 2 and ≥ 3 for patients aged < 75 and ≥ 75 years, respectively; and (5) with informed consent signed by them or their guardian.

### Exclusion criteria

Patients were excluded if (1) their cognitive dysfunction was caused by other conditions (including vascular dementia, Lewy body dementia, hormonal or metabolic abnormalities, hypothyroidism, VB12 or folic acid deficiency, delirium, or other affective and mental disorders); (2) they had severe chronic diseases, including heart disease, liver, and kidney disease, and hematopoietic system disease; (3) they were unable to cooperate with the study examinations due to aphasia, confusion, or other reasons; (4) they were taking anticoagulant drugs, including warfarin or heparin; and (5) if they had undergone acupuncture treatment within the previous 2 weeks.

### Termination criteria

In the process of clinical research, if the subject has a serious adverse event or adverse reaction, the trial will be suspended if the subject and researcher have discussed the situation and together agree that the subject cannot continue. In addition, if during the clinical research process, the subject felt that they lacked efficacy they would be given the option of suspending the trial.

### Drop out criteria

The following shedding standards were used to withdraw patients from the study. (1) Subjects who received other treatments of AD drugs during the study period; (2) subjects who did not come to the hospital for follow-up visits on time, and could not be contacted by telephone or SMS; and (3) subjects unwilling to continue to participate in the study, and who voluntarily withdraw their informed consent.

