### Interventions

This RCT will recruit 184 patients with mild-to-moderate AD and randomly allocate them to two groups: AG and CG. The AG (*n* = 92) will be treated using acupuncture combined with donepezil hydrochloride 5 mg/day for 12 weeks, while the CG (*n* = 92) will only receive donepezil hydrochloride 5 mg/day for 12 weeks. The two groups will undergo routine clinical treatment throughout the follow-up period. The evaluation time points will be the 12th week, 24th week (follow-up), and 36th week (follow-up) after treatment begins.

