#### Medicine treatment

Patients will receive donepezil hydrochloride 5 mg daily for 12 weeks. During the trial, participants will be prohibited from using other medicines for AD. The test drug was allocated based on the random coding sequence of the test drug and the number of cases. Each research unit will have a trial medication administrator. The investigator will screen qualified participants. After informed consent and writing of the study medical record, the trial medication administrator will arrange participants based on the order of patient visits and drug coding from small to large distributed medicines; further, they will be registered in the “Clinical Trial Drug Use Record Form.”

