#### Follow-up

All participants will be treated for 12 weeks. Subsequently, they will enter a 24-week follow-up period. In the 24th and 36th weeks, the patients will be reassessed using the MMSE, Alzheimer’s Disease Cooperative Study-Activities of Daily Living (ADCS-ADL) scale, and Quality of Life-Alzheimer’s Disease (QOL-AD) scale.

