### Outcome measures

Efficacy scores are performed by clinical neurologists and psychiatrists, who are trained by Shanghai Mental Health Center. Each time the scoring is performed by two scorers separately, if their results are inconsistent, the third scorer will make a ruling. All raters do not know the group of patients at the time of scoring. Table 2 shows the intervention and assessment time points to be used during the study period.

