### Statistical methods

All statistical analyses will be performed using SPSS Statistics for Windows V21.0 (IBM SPSS). Three sets of data will be used:Full analysis test (FAS). This will include all randomized cases that underwent assessments at least once for efficacy analysis. Missing data, which may affect analysis, will be supplemented using the last observation data. FAS will be the main population for efficacy evaluation.The protocol set (PPS, per-protocol set). This will include patients that meet the inclusion criteria specified in the trial protocol, complete all observation period plans, and do not use other drugs or treatment measures that may affect efficacy evaluation during the trial period. Efficacy evaluation will be conducted using the FAS and PPS. PPS is a secondary population for efficacy evaluation.Safety analysis data set (SS, safety set). This will include all cases that use the study drug at least once and undergo post-treatment safety evaluation after randomization. The SS will be the main population for safety evaluation.

All statistical tests will be performed as two-sided, and the statistical significance will be set at *p*<0.05. Quantitative indicators will be described using the mean and standard deviation, maximum value, minimum value, and median; moreover, the classification indicators will be described using the number and percentage. For counting data, two-sample tests (including the Cochran-Mantel-Haenszel test) or Fisher’s exact probability method will be used for between-group comparisons; moreover, measurement data will be expressed as mean and standard deviation. One-way analysis of variance will be used for among-group comparisons; additionally, the least significant difference method (LSD-t test) will be used for between-group comparisons.

Demographics (age, sex, duration of illness, education level) and MMSE scores will be compared between the two groups as baseline assessments. The main time point for efficacy evaluation is 12 treatment weeks (for PPS), as well as when the group is discontinued (for the FAS population). The *t*-test will be used for between-group comparisons of other measured efficacy indicators, including analyzing the change from the baseline. The ADAS-cog, MMSE, ADCS-ADL, and QOL-AD will be analyzed using the covariance analysis model for between-group comparisons with the baseline.

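### Taking another AD drug ends study participation rather than just trial treatment, and the week-12 per-protocol set depends on events up to week 36

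*Protocol article*

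**What the plan says.** Drop out criteria introduces its list with "The following shedding standards were used to withdraw patients from the study", and the first item is "Subjects who received other treatments of AD drugs during the study period". The consequence is leaving the study, not only stopping the trial treatment.

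The period is not formally defined. Outcome measures uses the same term for the whole assessment schedule: "Table 2 shows the intervention and assessment time points to be used during the study period". The Fig. 1 caption and the Interventions section put the assessments at weeks 12, 24 and 36. The Follow-up section says of participants who finish the 12 weeks: "Subsequently, they will enter a 24-week follow-up period".

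Three further statements bear on the point:

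- Medicine treatment: "During the trial, participants will be prohibited from using other medicines for AD". No end date is attached.
- Interventions: "The two groups will undergo routine clinical treatment throughout the follow-up period". What this care may contain is not stated.
- Statistical methods: PPS members must "complete all observation period plans, and do not use other drugs or treatment measures that may affect efficacy evaluation during the trial period". The same section names week 12 as the main PPS time point.

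The FAS is the main efficacy population and uses last observation carried forward; the PPS is secondary. The ethics and consent section keeps data gathered before a participant leaves. It makes no provision for assessments afterwards.

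**The concern.** Starting another AD drug is a post-randomisation event that may depend on how the patient is doing and, since the control arm has no sham procedure, on knowing the allocation. If it ends follow-up, the outcomes lost are probably not a random sample. Carrying forward an earlier score replaces what happened after the switch with a value from before it. For weeks 24 and 36 this can hide later decline in exactly those participants.

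The PPS raises a different problem. Membership of a week-12 comparison is decided partly by what happens in weeks 12–36. Someone treated and assessed as planned to week 12 drops out of that comparison by missing week 36, or by receiving another drug at, say, week 20. That is selection on the future, and it can shift the estimate if the later events are related to response and differ between arms.

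**Working it through.** **Which outcomes the withdrawal rule reaches.** The Abstract gives efficacy assessments at baseline and weeks 12, 24 and 36.

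| Other AD drug started | Week-12 FAS value | Week-24 and week-36 FAS values | In the week-12 PPS? |
|---|---|---|---|
| Before week 12 | Baseline or a score taken at discontinuation, carried forward | Carried forward | No |
| Weeks 12–24 | Observed and kept | Carried forward | No, although weeks 0–12 were as planned |
| Weeks 24–36 | Observed and kept | Week 24 kept, week 36 carried forward | No, although weeks 0–12 were as planned |

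In the first row, if the FAS requirement of at least one assessment means one after baseline, the participant may not be in the FAS at all.

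**The plan's own figure.** Sample size calculation gives mean changes of 2.32 (SD 2.02) for control and 4.04 (SD 4.23) for acupuncture. I read both as improvements, as the Background does for the second. The difference is 4.04 − 2.32 = 1.72. The root-mean-square SD is √((2.02² + 4.23²)/2) = 3.31. Then n = 2 × 3.31² × (1.960 + 1.282)² / 1.72² = 78.04, so 79 per group; the noncentral t gives 80, as stated. Also 80 × 1.15 = 92 per group, or 184. The sample size is not affected by this point.

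**What exclusion could do to the week-12 PPS (all rates assumed).** Let r be the share of an arm excluded for a later drug, and ρ the correlation between a poor week-12 change and later exclusion. Under a normal model the mean improvement of those retained rises by ρ × SD × k(r), where k(r) = φ(z_r)/(1 − r) and z_r is the r-quantile of the standard normal. This gives k(0.10) = 0.195, k(0.20) = 0.350 and k(0.30) = 0.497.

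PPS difference = 1.72 + ρ × (SD_A × k(r_A) − SD_C × k(r_C)), with A for acupuncture and C for control.

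Worked case: r_C = 0.20, r_A = 0.10, ρ = 0.3, common SD 3.31 gives 1.72 + 0.3 × 3.31 × (0.195 − 0.350) = 1.57.

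| Excluded, control / acupuncture | Common SD 3.31, ρ = 0.3 to 0.6 | Plan's SDs (2.02 and 4.23), ρ = 0.3 to 0.6 |
|---|---|---|
| 20% / 20% | 1.72 to 1.72 | 1.95 to 2.18 |
| 20% / 10% | 1.57 to 1.41 | 1.75 to 1.79 |
| 30% / 10% | 1.42 to 1.12 | 1.67 to 1.61 |
| 10% / 0% | 1.53 to 1.33 | 1.60 to 1.48 |

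Simulation of the common-SD case agrees to within 0.01 for the first three rows. Excluding poorly responding controls shrinks the difference, as the last row shows alone. Excluding poor responders from the acupuncture arm enlarges it, and more so if that arm is more variable, as the planning SDs imply.

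**Loss of numbers.** Power is Φ(1.72/(3.31 × √(2/n)) − 1.96). From 92 per group it is 94.1%; excluding 10%, 20% or 30% leaves 83, 74 or 64 per group and 91.7%, 88.4% or 83.5%. From 78 per group (92 less 15%) the sequence is 90.0%, 86.6%, 82.4%, 77.7%.

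**The case against.** The strongest reply is that the primary result is largely protected. It is the week-12 FAS comparison, and data from before withdrawal are kept, so a drug started in follow-up cannot alter a week-12 score already recorded. That stands. A reader might infer that switching during follow-up biases the primary analysis; the document does not support this. Only switches in the first 12 weeks matter there.

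A second reply is that the statements on follow-up treatment need not collide. The restriction concerns drugs other than donepezil, routine care is undefined, and the Discussion presents donepezil alone as meeting clinical guidelines. Care without a further AD drug would satisfy every section. This also stands: a reader might infer a flat contradiction, but what the text shows is an ambiguity. It still matters, because a site cannot tell whether a participant given another AD drug in routine care is within the protocol or must be withdrawn.

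Third, it is an inference that switchers are the deteriorating patients and that controls switch more often. The article says neither. It does let participants stop when "the subject felt that they lacked efficacy they would be given the option of suspending the trial", which shows that leaving may follow perceived response, but it says nothing about how this differs between arms.

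Finally, the PPS is secondary, and its details are often set out in an analysis plan. The first limits the weight of the point. The second does not remove it, because the article states the definition and the definition as stated has this flaw.

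**Conclusion.** The point holds in two parts. First, the rule on other AD drugs discards assessments that are already scheduled and replaces them with earlier scores. It affects the week-24 and week-36 secondary outcomes, and the week-12 primary analysis only for switches before week 12. Second, the week-12 PPS depends on events after week 12, so it can be biased if those events are related to response and differ in frequency or effect between arms.

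Both parts rest on reading the study and trial periods as running to week 36. That is the natural reading, but the terms are not defined. The size cannot be fixed from the document because no switching rate is given. In the cases tabulated, a true 1.72 appears as 1.12 to 2.18. A reader might infer that the bias favours acupuncture; the document does not support any fixed direction, and more switching among poorly responding controls would by itself shrink the estimated effect. The changes should be made, but the point does not overturn the primary analysis.

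**What to change.** - In Drop out criteria, separate stopping trial treatment from leaving the study. A participant who receives another AD drug keeps the week-12, 24 and 36 assessments still due and is analysed as randomised in the FAS, using the observed scores.
- In Statistical methods, define the week-12 PPS by eligibility, completion and treatment received in weeks 0–12 only.
- State the time window of the other-drug rule, and reconcile Drop out criteria, Interventions and Medicine treatment on which treatments are allowed during follow-up. Which rule is right is for the investigators.

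The cost is a protocol clarification, and the visits already exist. The FAS estimate will then include the effect of off-protocol drug use and may be slightly diluted. Timing matters for the first change, since outcomes not collected after withdrawal cannot be recovered at analysis. The PPS definition can still be corrected at any time before the data are analysed by group.
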